## Abstract

**Background:**

Despite recent technical advances in the management of acute kidney injury (AKI), such as continuous renal replacement therapy (CRRT), intensive care unit mortality is still high, at approximately 40 to 50%. Although several factors have been reported to predict mortality in AKI patients, fluid overload (FO) during CRRT is a well-known predictor of patient survival. However, FO has been mostly quantified as an arithmetical calculation and determined on the basis of the physicians’ perception. Even though such quantification and assessment provides an easy evaluation of a patient’s fluid status and is a simple method, it is not applicable unless a detailed record of fluid monitoring is available. Furthermore, the method cannot differentiate excess water in individual water compartments but can only reflect excess total body water. Bioimpedance analysis (BIA) has been used to measure the nutritional component of body composition and is a promising tool for the measurement of volume status. However, there has been no prospective interventional study for fluid balance among CRRT-treated AKI patients using BIA. Therefore, we will investigate the usefulness of fluid management using the InBody S10 (InBody®, Seoul, Korea), a BIA tool, compared with that of generally used quantification methods.

**Methods/design:**

This will be a multicenter, prospective, randomized controlled trial. A total of 244 patients undergoing CRRT treatment will be enrolled and randomly assigned to receive either to InBody S10-guided management or to fluid management based only on clinical information for 7 days. The primary outcome is to compare the rate of euvolemic status 7 days after the initiation of CRRT, with a secondary outcome being to compare the 28-, 60-, and 90-day mortality rates between the two groups.

**Discussion:**

This will be the first clinical trial to investigate the effect of using BIA-guided fluid management to achieve euvolemia in CRRT-treated AKI patients.

**Trial registration:**

ClinicalTrials.gov, ID: NCT03330626. Registered on 6 November 2017.

**Electronic supplementary material:**

The online version of this article (10.1186/s13063-018-3056-y) contains supplementary material, which is available to authorized users.

## Background

Continuous renal replacement therapy (CRRT) has been established to manage the excretion of toxins and the balance of electrolytes and fluids in critically ill patients with acute kidney injury (AKI) [1–4]. Despite technical advances in the management of AKI over the past few years [5, 6], intensive care unit (ICU) mortality is still high at approximately 40 to 50% [7–10]. Although several factors have been reported to predict mortality in AKI patients [7, 8], fluid overload (FO) at the initial time of CRRT is a well-known predictor of patient survival [7, 11–16]. A few recent studies have examined the effect of fluid accumulation on mortality: Neyra et al. [14] showed that higher cumulative fluid balance during 72 h of ICU admission was independently associated with hospital mortality regardless of AKI or chronic kidney disease (CKD) presence; in the Randomized Evaluation of Normal vs. Augmented Level of Replacement Therapy (RENAL) study, a negative mean daily fluid balance was consistently related to improved clinical outcomes [15]; and Garzotto et al. [16] emphasized the association between the severity and speed of fluid accumulation and ICU mortality.

However, FO has been mostly quantified as an arithmetical calculation: the difference between the sum of daily fluid intake and total output adjusted by body weight and determined based on the physician’s perception. Even though such quantification and assessment is an easy mechanism to evaluate a patient’s fluid status and is a basic method, it is not applicable unless a detailed record of the fluid monitoring is available, and it cannot differentiate water excess in individual water compartments; instead, the method can only reflect excess total body water (TBW) [17].

Bioimpedance analysis (BIA) has been used to measure the nutritional part of body composition, such as fat mass or fat-free mass (FFM), in diverse conditions [18, 19]. However, it has been used as a promising tool for the measurement of volume status [20]. With the electrical properties of body tissues, multifrequency-BIA (MF-BIA) differentiates extracellular water (ECW) or intracellular water (ICW) from TBW using different frequencies: 0, 1, 5, 50, 100, 200, 500 or 1000 kHz [21, 22]. To date, several studies have demonstrated the accuracy and clinical usefulness of MF-BIA in chronic hemodialysis or peritoneal dialysis patients [23–27]. Moreover, in critically ill patients, MF-BIA has been useful in assessing volume status [28] and net fluid removal using CRRT to successfully reduce TBW, ECW, and ICW [29]. Rhee et al. [17] investigated the effect of MF-BIA-defined volume status on the mortality of critically ill patients with AKI; the authors demonstrated that MF-BIA-defined excess volume parameters adjusted for the square of the patient’s height (H^2^), such as TBW/H^2^ and ICW/H^2^, were independently associated with higher in-hospital mortality in male patients with AKI undergoing CRRT. However, there has been no prospective interventional study for fluid balance among CRRT-treated AKI patients using the abovementioned BIA. Therefore, in this study, we will investigate the usefulness of fluid management using InBody S10 (InBody®, Seoul, Korea), a BIA tool, and compared with a generally used quantification method.

## Methods/design

### Hypothesis

BIA-guided fluid management will reach an euvolemic status in patients who are treated with CRRT better than fluid management guided by a generally used quantification method, which is calculated by the difference between the sum of daily fluid intake and total output adjusted by body weight and determined based on the physician’s perception. Moreover, the patients who achieve a euvolemic status 7 days after the initiation of CRRT will have better clinical outcomes based upon 28-, 60-, and 90-day mortality than those of patients who are still in a higher-volume status at the same time.

### Study design

This will be a multicenter, prospective, parallel-group, open-label, randomized controlled trial. It is an investigator-initiated clinical trial. We have followed the Standard Protocol Items: Recommendations for Interventional Trials (SPIRIT) 2013 Statement which defines standard protocol items for clinical trials (Additional file 1). The overall study algorithm is depicted in Fig. 1 and the SPIRIT and study schedule are given in Fig. 2. After enrollment, InBody S10 (InBody®, Seoul, Korea) will be used to measure fluid status at 0, 1, 2, and 7 days after the initiation of the CRRT in InBody S10-based fluid management group, but at 0 and 7 days in fluid management guided by a generally used quantification method. Physicians will not know the results of the InBody S10 measurement. Instead, another investigator will measure the InBody S10 and record the results. In the treatment group, the fluid monitoring will be managed according to Table 1, while the fluid balancing of the control group will be conducted based on the clinical information obtained by the physician, such as body weight, hemodynamic stability and daily intake and output. Clinical information including hemodynamic monitoring and laboratory data will be collected on the same days, and we will investigate the 28-, 60-, and 90-day survival status.

**Fig. 1 Fig1:**
[figure not shown]
The overall study algorithm. After enrollment, InBody S10 (InBody®, Seoul, Korea) will be used to measure fluid status at 0, 1, 2, and 7 days after the initiation of the continuous renal replacement therapy (CRRT) in InBody S10-based fluid management group, but at 0 and 7 days in fluid management guided by a generally used quantification method. Abbreviations: *AKI* acute kidney injury, *CRRT* continuous renal replacement therapy, *D0* the day of CRRT initiation, *D1*, *2 and 7* 1, 2 and 7 days from the day of CRRT initiation, respectively

**Fig. 2 Fig2:**
[figure not shown]
Schedule of enrollment, interventions, and assessments according to the Standard Protocol Items: Recommendations for Interventional Trials (SPIRIT) guideline. Abbreviations: *TBW* total body water, *ICW* intracellular water, *ECW* extracellular water, *TBW/H*^*2*^ total body water/height^2^

**Table 1 Tab1:** The guideline of fluid management for treatment group

TBW/H^2^ at D0, D1, D2	Target fluid removal amount (L/H^2^/day)	
13–14	−0.5	Or 1 L/day
14–15	−0.5	
15–16	−0.6	
16–17	−0.6	
17–18	−0.7	
18–19	−0.7	
19–	−0.7	

Fluid removal will be determined based on the TBW/H^2^ for 3 days (D0, D1, D2). However, fluid will be removed by 1 L/day if calculated fluid removal from the TBW/H^2^ is over 1 L/day

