### Study participants and measurements

All patients will be selected from among patients who must be treated with CRRT in four tertiary hospitals in Korea (Seoul National University Bundang Hospital, Seoul National University Hospital, Seoul National University Boramae Medical Center, and Ewha Womans University Mokdong Hospital). Patients aged over 18 years who require CRRT for AKI will be screened for study participation according to the inclusion and exclusion criteria presented in Table 2.

**Table 2 Tab2:** Inclusion and exclusion criteria

Inclusion criteria	
Patients will be eligible for *inclusion* in the study if *all* the following criteria are met:	
1. The treating clinician believes that the patient requires continuous renal replacement therapy for acute kidney injury	
2. The treating clinicians anticipate treating the patient with continuous renal replacement therapy for at least 72 h	
3. Informed consent has been obtained	
4. The patient fulfills one of the following clinical criteria for initiating continuous renal replacement therapy:	
Urine output < 100 mL/6 h that has been unresponsive to fluid resuscitation measures	
K^+^ > 6.5 mmol/L	
pH < 7.2	
Urea > 25 mmol/L	
Clinically significant organ edema in the setting of acute kidney injury	
5. Patients who are over 5% of fluid overload or their total body water/height^2^ ≥ 13 L/m^2^	
Exclusion criteria	
Patients will be *excluded* from the study if, in the opinion or knowledge of the responsible clinician *any* of the following criteria are present:	
1. Patient age is < 18 years	
2. Death is imminent (< 24 h)	
3. There is a strong likelihood that the study treatment will not be continued in accordance with the study protocol.	
4. The patient has been treated with continuous renal replacement therapy or other dialysis previously during the same hospital admission.	
5. The patient has been on maintenance dialysis prior to the current hospitalization.	
6. Any other major illness that, in the investigator’s judgment, will substantially increase the risk associated with the subject’s participation in this study.	

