### Outcome measures

The primary outcome is to compare the rate of euvolemic status at 7 days from the CRRT start. The euvolemic status will be considered different when TBW/H^2^ between the day of CRRT initiation (D0) and 7 days from the day of CRRT initiation (D7) is less than − 2.1 or TBW/H^2^ at D7 is less than 13 L/m^2^. According to Rhee’s recent study, the group reaching TBW/H^2^ < 13 L/m^2^ had a significantly enhanced survival rate compared with that of the group that could not reach TBW/H^2^ < 13 L/m^2^ [17]. Moreover, our further study has revealed that the survival rate was significantly increased when the difference in TBW/H^2^ between CRRT initiation and at 7 days from CRRT start (TBW/H^2^
_at 7days_ – TBW/H^2^
_at CRRT initiation_) was less than − 2.1 L/m^2^, even though it was not sufficient to reach TBW/H^2^ < 13 L/m^2^ (data not shown). Therefore, we will also consider the euvolemia as TBW/H^2^
_at 7days_ – TBW/H^2^
_at CRRT initiation_ < − 2.1 L/m^2^ in this study. The secondary outcome is to investigate the 28-, 60-, and 90-day mortality rates in the control and treatment groups and to compare the mortality rates between the groups that reach euvolemic status or not for sub-analysis.

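### The 1 L/day cap under Table 1 overrides every band above a height of 1.41 m, so at TBW/H² of 13 or more the BIA reading does not grade the removal target

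*Protocol article*

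**What the plan says.** Table 1 of the protocol article sets removal in the treatment arm under the column heading "Target fluid removal amount (L/H^2^/day"). The entries are 0.5 for TBW/H² of 13 to 15, 0.6 for 15 to 17 and 0.7 for 17 and above, spread over seven rows. No row covers a reading below 13. The footnote gives the period, "Fluid removal will be determined based on the TBW/H^2^ for 3 days (D0, D1, D2"), and the cap, "fluid will be removed by 1 L/day if calculated fluid removal from the TBW/H^2^ is over 1 L/day". The table body also prints a 1 L/day alternative beside the first row.

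The abstract describes the control arm as "fluid management based only on clinical information for 7 days"; that sentence appears to give the period for both arms. The article states no BIA rule for D3 to D7.

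Under Outcome measures, "The primary outcome is to compare the rate of euvolemic status at 7 days from the CRRT start". Euvolemia is met in either of two ways: a D0-to-D7 change in TBW/H² below −2.1 L/m², "or TBW/H^2^ at D7 is less than 13 L/m^2". The change criterion is an added route, because survival was reported to be better after such a fall "even though it was not sufficient to reach TBW/H^2^ < 13 L/m^2^ (data not shown").

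**The concern.** The hypothesis is that BIA-guided management reaches euvolemia better than usual management. The Study design section sends the treatment arm to Table 1, and both Study design and Assessment of the fluid status keep physicians blind to the readings. The Table 1 target is therefore the only stated channel from reading to care. If the cap binds in every row, that channel carries the same number for every reading of 13 or more, and the graded guidance that the arm is named for is lost. A positive or negative result would then be credited to graded BIA guidance that was not delivered.

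A second mismatch follows. The tabulated targets cover three days, while one of the two endpoint criteria is a fixed fall in TBW/H². The targets should be checked against that fall.

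**Working it through.** **Inputs.** Bands r = 0.5, 0.6 and 0.7 L/m² per day, the cap of 1 L/day and the three days D0 to D2 come from Table 1 and its footnote. The criteria of −2.1 and 13 L/m² come from Outcome measures. Heights are not given, so 1.45 to 1.80 m is an assumed range. Net removal is assumed to equal the fall in TBW, with no other gains or losses.

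**The plan's own figure.** The article computes no delivered volume. Its only computed design figure is the sample size. Its last step reproduces: 97/(1 − 0.20) = 121.25, rounded up to 122 per group. Nothing below depends on it.

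**Step 1: where the cap binds.** Calculated removal is r × H². It exceeds 1 L/day when H > √(1/r).
- r = 0.5: H > √2 = 1.414 m
- r = 0.6: H > 1.291 m
- r = 0.7: H > 1.195 m

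Above 1.414 m all seven rows are capped. If the entries were instead read as litres per day without H², none would exceed 0.7 and the cap would never act. That reading also contradicts the column's unit.

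**Step 2: what each band asks for and what three capped days deliver.** The three-day fall in TBW/H² is 3/H². The highest D0 value from which that fall reaches 13 is 13 + 3/H².

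| Height (m) | H² | Bands 0.5 / 0.6 / 0.7 (L/day) | After cap (L/day) | Three-day fall (L/m²) | D0 limit for the <13 route |
|---|---|---|---|---|---|
| 1.45 | 2.10 | 1.05 / 1.26 / 1.47 | 1 | 1.43 | 14.43 |
| 1.60 | 2.56 | 1.28 / 1.54 / 1.79 | 1 | 1.17 | 14.17 |
| 1.70 | 2.89 | 1.445 / 1.73 / 2.02 | 1 | 1.04 | 14.04 |
| 1.80 | 3.24 | 1.62 / 1.94 / 2.27 | 1 | 0.93 | 13.93 |

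At 1.70 m the delivered rate is 1/2.89 = 0.35 L/m² per day, against 0.5 to 0.7 tabulated.

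**Step 3: the change criterion.** Three capped days pass −2.1 only if 3/H² > 2.1, that is H < √(3/2.1) = 1.195 m. Without the cap, three days give 3 × 0.5 = 1.5, 3 × 0.6 = 1.8 and 3 × 0.7 = 2.1 L/m². The top band equals 2.1 and does not pass a strict inequality, so the cap is not the only cause of the shortfall.

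**Step 4: how much the period matters.** If 1 L/day continued for seven days, which the article does not say, the fall would be 7/H²: 2.73 at 1.60 m, 2.42 at 1.70 m and 2.16 at 1.80 m. It would pass 2.1 for any height below √(7/2.1) = 1.826 m.

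**The case against.** The strongest reply is that a cap on a dosing table is ordinary, and that three guided days fit inside a seven-day period. Readings are scheduled only on D0, D1, D2 and D7, so removal can be set by BIA on three days and by other means afterwards. Management of D3 to D7 is also detail that a journal article may leave to the full protocol. This stands as far as it goes: the two durations are unclear rather than plainly incompatible. It does not rescue the bands, because a cap that binds in every row leaves nothing for the rows to grade.

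A second reply is that the table was read by a program, and that the 1 L/day entry sits beside the 13–14 row only, perhaps as a merged cell. If the cap applied to that row alone, the higher bands would still differ. The footnote, however, is worded for any calculated removal. If the narrower meaning was intended, the footnote needs correcting.

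A reader might infer more than the article supports:
- *The reading never affects care.* Not shown. Eligibility reads "Patients who are over 5% of fluid overload or their total body water/height^2^ ≥ 13 L/m^2", so a patient can enter below 13, and a D1 or D2 reading can fall below it. No row exists there, so the reading may still switch removal on or off.
- *The endpoint cannot be reached.* Not shown. The −2.1 criterion is one of two routes, and removal on D3 to D7 counts towards the D7 value.
- *Most patients fall short, or the assumed 19-point difference is undermined.* Not shown. The article gives no D0 distribution of TBW/H², no heights, no base rate and no control-arm removal, and one arm's arithmetic does not settle a difference between arms.

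**Conclusion.** Wrong as written, in a limited form. Table 1 and its footnote contradict each other: above 1.414 m the cap replaces all seven bands with one number. Among readings of 13 or more, the BIA value then does not change the removal target for practically any adult. This rests only on the printed unit, the general wording of the footnote and adult height.

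The three tabulated days also fall short of the change criterion on their own: 0.93 to 1.17 L/m² at 1.80 to 1.60 m with the cap, and at most exactly 2.1 without it. This second part is less certain. It assumes that removal equals the fall in TBW, and it counts nothing on D3 to D7. Within the same three capped days, the route through a D7 value below 13 remains open from a D0 value below about 13.9 to 14.2 at those heights.

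**What to change.** Reconcile four items in one amendment: the Table 1 bands, the footnote cap, the guided period (three days in the table, seven in the abstract) and the two D7 criteria. Support it with a one-page tabulation of the daily and cumulative volume that each row delivers by height, for example 1.45 to 1.85 m. Use it to confirm that the reading changes what is delivered and to show how the targets relate to each D7 criterion. State what applies to readings below 13 and on D3 to D7, or point to where the full protocol says so.

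If the cap stands as written, describe the intervention and the trial's conclusion as a fixed 1 L/day target at TBW/H² of 13 or more versus usual care, not as graded BIA-guided removal. Which removal rule is right is for the investigators; none is proposed here.

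The cost is an amendment to the table, its footnote and the duration wording, plus the arithmetic check. No extra patients are needed. Because the article reports recruitment as ongoing, patients treated under the present wording should be identifiable in the analysis if the rule changes.

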### Study participants and measurements

All patients will be selected from among patients who must be treated with CRRT in four tertiary hospitals in Korea (Seoul National University Bundang Hospital, Seoul National University Hospital, Seoul National University Boramae Medical Center, and Ewha Womans University Mokdong Hospital). Patients aged over 18 years who require CRRT for AKI will be screened for study participation according to the inclusion and exclusion criteria presented in Table 2.

**Table 2 Tab2:** Inclusion and exclusion criteria

Inclusion criteria	
Patients will be eligible for *inclusion* in the study if *all* the following criteria are met:	
1. The treating clinician believes that the patient requires continuous renal replacement therapy for acute kidney injury	
2. The treating clinicians anticipate treating the patient with continuous renal replacement therapy for at least 72 h	
3. Informed consent has been obtained	
4. The patient fulfills one of the following clinical criteria for initiating continuous renal replacement therapy:	
Urine output < 100 mL/6 h that has been unresponsive to fluid resuscitation measures	
K^+^ > 6.5 mmol/L	
pH < 7.2	
Urea > 25 mmol/L	
Clinically significant organ edema in the setting of acute kidney injury	
5. Patients who are over 5% of fluid overload or their total body water/height^2^ ≥ 13 L/m^2^	
Exclusion criteria	
Patients will be *excluded* from the study if, in the opinion or knowledge of the responsible clinician *any* of the following criteria are present:	
1. Patient age is < 18 years	
2. Death is imminent (< 24 h)	
3. There is a strong likelihood that the study treatment will not be continued in accordance with the study protocol.	
4. The patient has been treated with continuous renal replacement therapy or other dialysis previously during the same hospital admission.	
5. The patient has been on maintenance dialysis prior to the current hospitalization.	
6. Any other major illness that, in the investigator’s judgment, will substantially increase the risk associated with the subject’s participation in this study.	

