### Sample size calculations

No previous report has evaluated the effect of InBody S10 (InBody®)-guided fluid management on CRRT-treated patients. We will randomly divide the enrolled participants equally into two groups. Assuming a 19% difference in the rate of achieving euvolemic status between the two groups with 0.8 of power, two-sided, and 0.05 of alpha, 97 participants will be allocated in each group. However, 122 participants will be required to enroll in each group due to a 20% withdrawal rate.

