So far, there is no definite index for determining euvolemic status. Instead, most physicians determine their patients’ volume status based on clinical information, such as intake and output, chest radiographic examination, and physical examination. Therefore, the fluid balance of patients may be managed differently based on the physicians’ opinions, even with the same patients. The abovementioned study by Rhee et al. [17] suggested that TBW/H^2^ and ICW/H^2^ were independently associated with higher in-hospital mortality in male patients with AKI undergoing CRRT, and the group reaching TBW/H^2^ < 13 L/m^2^, which was 13% of total enrolled patients, had a significantly increased level of survival compared to that of other patients. Thus, we will define the euvolemia as the status of TBW/H^2^ < 13 L/m^2^. In addition, our study of fluid removal has revealed that the difference in TBW/H^2^ between CRRT initiation and at day 7 of CRRT,[(BW/H^2^
_at 7days_ – TBW/H^2^
_at CRRT initiation_), especially when it was greater than − 2.1 L/m^2^, was significantly associated with an increased mortality rate, even though it did not reach TBW/H^2^ < 13 L/m^2^ (data not shown). Therefore, we will also consider another measure of euvolemia in this study, namely TBW/H^2^
_at 7days_ – TBW/H^2^
_at CRRT initiation_ < − 2.1 L/m^2^.

There is a chance that patients within the same institution will be correlated more closely than patients at different institutions will. To avoid this issue, we will investigate for the possible clustering of patients at the recruitment institution level and will accommodate such clustering in our models and analysis as required. We have also conservatively calculated the sample size, assuming a high drop-out rate, to overcome this potential problem.

There are a few limitations in this study. First, this study will be investigated in Korean Tertiary Hospitals, which means that the results will require cautious interpretation concerning ethnicity. Second, we have defined euvolemia arbitrarily, although this definition was based on recent data and upon our own study. However, this study is the first study, to the best our knowledge, to determine guidelines for the fluid balance in CRRT-treated critically ill AKI patients using a prospective randomized controlled trial. We expect that the endpoint of the VENUS study will provide the utmost information to healthcare providers.

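### Inclusion criterion 5 admits patients already below the trial's own euvolemia threshold; for them the primary endpoint does not measure reaching euvolemia, and the treatment effect may be diluted

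*Protocol article*

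**What the plan says.** All of the following is in the protocol article.

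- **Eligibility** (Study participants and measurements, Table 2, criterion 5): "Patients who are over 5% of fluid overload or their total body water/height^2" at or above 13 L/m². Either route is enough. No other inclusion or exclusion criterion sets a floor on TBW/H².
- **Primary endpoint** (Outcome measures): a patient is euvolemic if TBW/H² changes by less than −2.1 L/m² from D0 to D7, or if "TBW/H^2^ at D7 is less than 13 L/m^2". The second limb carries no condition on the D0 value.
- **Definition of euvolemia** (Discussion): "we will define the euvolemia as the status of TBW/H^2^ < 13 L/m^2".
- **Intervention** (Table 1, "The guideline of fluid management for treatment group"): the lowest row is 13–14. The footnote says "Fluid removal will be determined based on the TBW/H^2^ for 3 days (D0, D1, D2").
- **Sample size** (Sample size calculations): "Assuming a 19% difference in the rate of achieving euvolemic status between the two groups with 0.8 of power, two-sided, and 0.05 of alpha", from which "97 participants will be allocated in each group". After a 20% withdrawal allowance this becomes 122 per group.
- **Analysis sets** (Statistical analyses): the ITT set is everyone randomised who completes the first visit, and the per-protocol set is everyone who completes the study. Neither set removes a patient because of the D0 reading.

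**The concern.** The two routes in criterion 5 measure different things. The Background and Discussion describe fluid overload as intake minus output relative to body weight, whereas TBW/H² is a bioimpedance reading. A patient can exceed 5% on the first and still read below 13 on the second.

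The Hypothesis section is about reaching euvolemia. A patient who enters below 13 is already there by the trial's definition. For that patient the endpoint records staying below the line, and it does so even when TBW/H² has risen. The guided arm has no stated removal target in that range, so the documents describe no mechanism by which the BIA guidance would separate the arms. If such patients succeed at similar rates in both arms, they add successes to each side and pull the difference towards zero.

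**Working it through.** **1. What the endpoint requires at each starting value.** The two limbs together amount to: success if D7 < max(13, D0 − 2.1).

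- D0 at or above 13: success always needs a fall, either to below 13 or by more than 2.1.
- D0 below 13: D0 − 2.1 is below 10.9, so the rule is simply D7 < 13. No fall is needed.

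Example: D0 = 11.0 and D7 = 12.9 is a success. At an assumed height of 1.65 m the gain is 1.9 × 1.65² = 1.9 × 2.7225 = 5.2 L.

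**2. The plan's own sample size.** The article gives the 19-point difference but no control rate, so 97 cannot be derived from the stated inputs alone. It is reproduced for some control rates. With 27% vs 46% and unpooled variance:

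n = (1.96 + 0.8416)² × (0.27 × 0.73 + 0.46 × 0.54) / 0.19² = 7.849 × 0.4455 / 0.0361 = 96.9, so 97.

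Withdrawal: 97 / 0.8 = 121.25, so 122; 2 × 122 = 244, as stated. The 27% is therefore an assumption consistent with the plan, not a figure from it.

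**3. Illustration of dilution.** Assumptions: 27% vs 46% among patients with D0 ≥ 13; success probability s = 80–90% at D7 in both arms among those below 13; a share f entering below 13; 97 analysed per arm. Then

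p₁ = (1 − f) × 0.27 + f × s, p₂ = (1 − f) × 0.46 + f × s, so Δ = 0.19 × (1 − f).

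Power (pooled two-proportion test, two-sided 0.05, p̄ the mean of p₁ and p₂) = Φ{[Δ√n − 1.96 √(2p̄(1 − p̄))] / √(p₁(1 − p₁) + p₂(1 − p₂))}.

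- f = 0: (0.19 × 9.849 − 1.96 × 0.6809) / 0.6675 = 0.804, power 79%.
- f = 10%, s = 80%: p₁ = 0.323, p₂ = 0.494, Δ = 0.171; (1.684 − 1.363) / 0.6846 = 0.470, power 68%.

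The last column applies the same formula to 27% vs 46% with only the 97 × (1 − f) patients per arm who start at or above 13.

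| Share below 13 at D0 | Difference (points) | Power, all 97 per arm | Power, D0 ≥ 13 only (n per arm) |
|---|---|---|---|
| 0% | 19.0 | 79% | 79% (97) |
| 2% | 18.6 | 77% | 78% (95.1) |
| 3% | 18.4 | 76% | 78% (94.1) |
| 5% | 18.05 | 73–74% | 77% (92.2) |
| 10% | 17.1 | 68% | 75% (87.3) |
| 20% | 15.2 | 56–57% | 69% (77.6) |
| 30% | 13.3 | 46% | 64% (67.9) |

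**4. Sensitivity to the equal-response assumption.** Suppose patients below 13 succeed in 60% vs 80% of cases. The overall difference is then 19 × (1 − f) + 20 × f, for example 19.1 points at f = 10%. Power stays at 77–78% for f = 10–30%, so the dilution nearly disappears.

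**The case against.** The case against a stronger claim is good, and most of it stands.

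- A reader might infer that these patients are successes on the day of randomisation. They are not. The endpoint is read at D7, so a patient below 13 at D0 satisfies the threshold at entry but succeeds only if still below it a week later.
- A reader might infer that the stated power is lost. The documents do not show this. They give no share entering below 13. The 13% in the Discussion describes a group reaching that level in an earlier cohort and is not clearly a baseline share. The 19-point difference is stated for the two groups without restriction, so it may already refer to the population as enrolled, in which case nothing is lost. Equal response below 13 is plausible given Table 1 but not proven, because control patients are managed on clinical information and care may still differ between arms.
- A reader might infer bias. Both randomised arms admit these patients on the same terms, so the comparison is valid under the null and type I error is not inflated.
- A reader might take restriction to D0 ≥ 13 as automatically safe because D0 is a baseline. Study design and the Fig. 1 legend place the InBody readings after enrolment, and nothing says that the D0 reading precedes randomisation.

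None of this removes the mismatch itself. Admitting patients on clinical overload is a legitimate choice, but the endpoint and Table 1 do not then fit everyone admitted.

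**Conclusion.** The point holds as an inconsistency between criterion 5, the primary endpoint and Table 1, and it follows from the text without any power calculation. For patients who enter below 13, the endpoint can score a fluid gain as success, and the guided arm has no stated target.

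The consequence is possible attenuation of the treatment effect, of a size that the documents cannot fix. A very small share below 13 would cost only 2–3 points of power; a share of 10% or more would matter (from 79% to 68% or lower). These figures depend on three assumptions: the 27% control rate, the 19-point difference applying only to patients at or above 13, and similar success in both arms below 13.

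**What to change.** 1. **Patients still to be enrolled** (the Trial status section says recruitment is ongoing): amend criterion 5 to require TBW/H² ≥ 13 L/m² on a reading taken before randomisation.
2. **Patients already enrolled:** define the primary endpoint analysis on randomised patients with D0 TBW/H² ≥ 13, provided that the D0 reading precedes randomisation or at least the start of arm-specific management. State that timing explicitly. Report the full randomised set alongside.
3. **Reconcile** criterion 5, the endpoint and Table 1. What fluid management applies below 13 is for the investigators to decide.

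Cost: protocol and analysis wording, a somewhat smaller primary set, or slightly slower enrolment. Restricting the set does not by itself restore 80% power; on the assumptions above it gives about 75%, 69% or 64% if 10%, 20% or 30% enter below 13. That is still more than the diluted full set gives under the same assumptions.
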